**8** **Methods** **Participants, Inclusion and exclusion criteria**:

*Randomized Controlled Trial (RCT)*

One hundred patients, 60 years of age and older, with an American Society of Anesthesiologists (ASA) classification of fitness of 3 or less, undergoing major elective abdominal or orthopaedic surgery under general anaesthesia at King’s College Hospital will participate in the study.

Inclusion criteria

(1)Patients over 60 years of age classified as ASA (American Society of Anesthesiologists) of three or less who were due to undergo major elective abdominal or orthopaedic surgery (2) Mini Mental State Examination (MMSE) score equal to or greater than 23. (3) Adequate English was a pre-requisite to enable consent and to undertake study assessments.

Exclusion criteria

(1) Unable to complete the outcome measures (2) A diagnosis of Alzheimer’s disease or other dementia (3) Individuals undergoing surgical procedures under regional anaesthetics.

Assessments

1/ Electrocardiography (ECG) and laboratory tests as clinically indicated.

2/ Cognitive evaluation: Global cognitive function (Cambridge Assessment for Mental Disorder in the Elderly, section B (CAMCOG-B - , Mini-Mental State Examination -MMSE), memory (CAMCOG memory subscale), executive function (Trail – Making task part A and B) and vigilance accuracy and vigilance reaction time from the Cognitive Drug Research battery as indices of attentional performance and cognitive processing speed pre-operatively, 1 week post surgery and 12 weeks post surgery.

Definitions of POCD and other criteria for cognitive dysfunction will be validated based upon an initial cohort study (appendix 1).

Randomisation

Participants will be randomized according torandomisation lists, stratified by age group (65 to 70, 70 to 75 and over 75) , which will be generated by the study statistician in the statistical program package R. Based upon the list, sealed envelopes containing the randomization codes will be delivered to the operating theatres, and an envelope selected randomly by the anaesthetist. The randomisation envelope will be opened only after the participant’s eligibility and willingness to participate are re-confirmed prior to surgery.

Blinding

The trial will be double blind with the patients, informants and researchers blind to treatment allocation.

Monitoring and Intervention

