A bispectral index (BIS) of the electroencephalogram will be used to monitor anaesthetic depth. The target BIS range will be 40-60 (±5).

During and until extubation after the procedure, rSO2 will be continuously monitored using SICO to enable interventions if regional cerebral saturations drop by more than 15% from baseline or to less than 50% intraoperatively, using the following algorithm

1. BP maintained within 10% of baseline value by giving fluids or inotropes to bring the value back to within these limits
2. SpO2 maintained above 95% by increasing the FIO2 to 50%
3. Maintain EtCO2 between 4·5 to 5·5%. avoiding excessive hypercarbia as well as hypocarbia.
4. If there is ongoing moderate to severe haemorrhage consider transfusion if the Hb level is less than 9g.dl-1

If all the above fail to correct a decline then increase the etCO2 to 6% and give 100% O2.

Intervention

In the intervention group the anaesthetist will have full access to the BIS and SICO data to optimize the depth of anesthesia and to identify and facilitate intervention to rectify cerebral oxygen desaturation. In the control group the BIS and SICO data will be collected, but the anaesthetist will be blind to the monitoring data.

Statistical methods

The study is powered as a pilot study. A cohort of 73 patients gives 80% power to the 5% level of significance to detect a between group difference of 0·33 SD. The goal is to enroll 100 participants to allow for drop-outs.

The primary efficacy population will be defined as all patients who were randomised to receive the intra-operative anesthetic intervention or treatment as usual and completed at least one follow-up assessment. Statistical analyses will be undertaken using the SPSS software, version 17.0 (SPSS, Chicago, IL, USA). Two-sided p values of less than 0·05 will be deemed to be statistically significant. A full statistical evaluation protocol will be developed by the study statistician.

Additional Objectives

Fifty age matched controls will be recruited in parallel, drawn from the spouses of people undergoing surgery. The pre-operative assessment will include a standardized evaluation to identify pre-existing delirium (Confusion Assessment Method CAM29) or significant cognitive impairment including MMSE <2530, and/or the presence of dementia (DSMIIIR criteria, American Psychiatric Association 1987). This will allow additional comparisons between post-operative patients and age matched controls to address hypotheses b-f.

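### The stated 80% power to detect 0.33 SD between groups with 73 patients does not hold for the two-arm comparison: power is about 28%, and 73 patients detect about 0.66 SD.

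*Protocol*

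**What the plan says.** All the planning inputs are in section 8 of the protocol.

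- Statistical methods, sample size: "A cohort of 73 patients gives 80% power to the 5% level of significance to detect a between group difference of 0·33 SD". The sentence before it reads "The study is powered as a pilot study", and the one after it "The goal is to enroll 100 participants to allow for drop-outs".
- Statistical methods, testing: "Two-sided p values of less than 0·05 will be deemed to be statistically significant".
- Participants: the randomised trial consists of "One hundred patients, 60 years of age and older". The total is therefore 100, and the 73 are the patients expected to remain after drop-out, over both arms.
- Intervention, and the definition of the efficacy population: there are two arms, the monitored intervention and usual care. Hypothesis (a) in section 7 compares them at 7 days and 3 months.
- Assessments: cognition is measured before surgery and at 1 and 12 weeks after it.

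The protocol gives no allocation ratio, outcome SD, correlation between visits or covariate-adjusted variance in support of the power figure. It leaves the full statistical evaluation to a later document.

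**The concern.** An effect of about a third of an SD is small for a parallel-group trial of this size, and 73 patients in total looked far too few for 80% power.

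This sentence is the only justification given for the sample size. Anyone relying on it would believe that a true difference of 0.33 SD would be missed 2 times in 10. On the stated inputs it would be missed about 7 times in 10. A non-significant result could then be given more weight against a 0.33 SD benefit than the data can bear. The protocol does not say that it would be read that way, but the stated power invites it.

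**Working it through.** **Inputs.** Effect 0.33 SD (so SD = 1), two-sided 5%, target power 80%, N = 73 evaluable and 100 enrolled, all from section 8. Assumption: 1:1 allocation, which is the most favourable for power. No baseline adjustment, since none is stated. Normal quantiles: 1.960 and 0.842, with sum 2.8016 before rounding.

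**Step 1: reproduce the plan's figure.** The two-arm formula does not give it. The one-sample (or paired) formula does:

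n = (1.960 + 0.842)² / 0.33² = 7.849 / 0.1089 = 72.07, rounded up to 73.

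Power of a one-sample test at n = 73: Φ(0.33 × √73 − 1.960) = Φ(0.860) = 80.5%. The t-based value is 79.4%.

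**Step 2: two-arm power at 0.33 SD.** With m patients per arm, power ≈ Φ(0.33 × √(m/2) − 1.960).

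| Reading | m per arm | Normal | t-based |
|---|---|---|---|
| 73 in total | 36.5 | Φ(−0.550) = 29.1% | 28.5% |
| 100 in total, no drop-out | 50 | Φ(−0.310) = 37.8% | 37.2% |
| 73 per arm | 73 | Φ(0.034) = 51.3% | 50.8% |

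One-sided testing, which the protocol does not plan, gives 40% with 73 in total and 63% with 73 per arm. Comparing 73 surgical patients with the 50 spouse controls gives 43%. No two-group reading comes near 80%.

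**Step 3: number needed at 0.33 SD.** m = 2 × 7.849 / 0.1089 = 144.1, so 145 per arm or 290 in total, about four times 73. The t-based solution is 145.1 per arm.

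**Step 4: difference detectable with 80% power.** d = 2.8016 × √(2/m).

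- 73 in total: 2.8016 × √(2/36.5) = 0.656; t-based 0.665. About 0.66 SD.
- 100 in total: 2.8016 × √(2/50) = 0.560; t-based 0.566. About 0.57 SD.

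**Step 5: what baseline adjustment could recover.** ANCOVA on one follow-up multiplies the SD by √(1 − r²), where r is the correlation between baseline and follow-up. The protocol gives no r, so these values are illustrations.

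- At an assumed r = 0.7, √(1 − 0.49) = 0.714. The detectable difference is 0.665 × 0.714 = 0.47 SD with 73 and 0.566 × 0.714 = 0.40 SD with 100.
- With 73 in total and one follow-up, normal-approximation power at 0.33 SD is 37%, 51% and 65% for r = 0.5, 0.7 and 0.8.
- To detect 0.33 SD with 73 patients, the residual variance must fall to (0.33/0.665)² = 0.246. One follow-up: r = √(1 − 0.246) = 0.87.
- Mean of both follow-ups, with equal correlations among the three visits: residual variance (1 + r)/2 − r² = 0.246, so r = 0.81.

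**Step 6: precision.** The unadjusted 95% CI half-width with 36 + 37 patients is 1.994 × √(1/36 + 1/37) = 0.47 SD, wider than the 0.33 SD target.

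**The case against.** **The study is a pilot.** This is fair as a caveat: a pilot need not be powered for efficacy, and quoting a power figure in a pilot is not in itself a contradiction. A reader might infer that the label and the power claim conflict. The document does not support that, and it is no part of this point. Nor does the label make the stated power correct.

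**The analysis may adjust for baseline and use both follow-ups.** This is the strongest objection. A reader might conclude that only a correlation near 0.87 could rescue the claim. That holds for a single follow-up; averaging the two planned follow-ups lowers the requirement to about 0.81 under equal correlations. So the claim could be true under some analysis. However, the protocol states no correlation, adjustment or averaging, and hypothesis (a) names the two time points separately.

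**The details belong in the statistical plan.** The choice of model does, and the protocol may leave it there. But the sentence at issue is not an omission. It is a figure stated in the protocol, and it is wrong on the inputs beside it.

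**The cause is not documented.** This stands. A reader might infer that a one-sample or paired formula was certainly used. The protocol names no formula. A factor-of-two slip in the effect size would fit about as well, since 0.66 SD with 73 in total gives 79.4% power. The conclusion does not depend on which it was.

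**Conclusion.** The point holds. For the two-arm, two-sided comparison, 73 patients in total give about 28% power at 0.33 SD, not 80%. All 100 give 37%. Reading 73 as per arm conflicts with the total of 100 and still reaches only 51%. The detectable difference at 80% power is about 0.66 SD with 73 and 0.57 SD with 100: with 73 patients it is twice the stated effect, which corresponds to a fourfold shortfall in numbers.

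This rests on 1:1 allocation and an unadjusted comparison. Unequal allocation would lower the power; baseline adjustment would raise it, by an amount that depends on a correlation the protocol does not give. The match with a one-sample or paired calculation is a likely explanation, not an established one.

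A reader might also infer that the enrolment target of 100 is itself wrong, or that the trial must grow to 290. That does not follow. A pilot of 100 can stand; the power attributed to it cannot.

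**What to change.** Replace the power sentence with, for example: *With 73 evaluable patients (about 36 per arm) the trial has 80% power, two-sided 5%, to detect 0.66 SD (0.57 SD if all 100 are evaluable).*

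Alternatively, plan a baseline-adjusted comparison (ANCOVA on the pre-operative score and age stratum, both already collected). Quote its power under a correlation that is stated and justified, and say whether it refers to one follow-up or the mean of both. The r = 0.7 figures above show the form such a statement would take; they do not supply the assumption.

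In either case, report the between-group estimate with its 95% confidence interval, so that a non-significant p value is not taken to exclude 0.33 SD.

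The cost is one rewritten paragraph and a less favourable stated detectable effect. No extra patients are needed.

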To evaluate whether monitoring and normalization of cerebral oxygen saturation (rSO2) minimizes intraoperative cerebral desaturation, 122 elderly patients undergoing major abdominal surgery with general anaesthesia were studied11. Patients were randomly allocated to an intervention group (the monitor was visible and rSO2 was maintained at > 75% of pre-induction values; *n* = 56) or a control group (the monitor was blinded and anaesthesia was managed routinely; *n* = 66). Cerebral desaturation (rSO2 reduction > 75% of baseline) was observed in 11 patients of the treatment group (20%) and 15 patients of the control group (23%) (*P* = 0.82). To assess whether cerebral desaturation was associated with POCD, the mini-mental state examination (MMSE) was assessed. Although there was no overall statistical difference in outcome (as assessed by reduction in MMSE between the two groups), those patients who suffered a cerebral desaturation had a significantly lower MMSE score at 7 days. A decline in cognitive function (defined as a reduction in MMSE => 2 points from baseline) during the first week after surgery was observed in 20 patients of the treatment group (35%) and 30 patients of the control group (54%) (*P* _ 0.137); however, when considering only those patients who actually had at least one episode of intraoperative desaturation in both groups, a decline in cognitive function was observed in 10 patients of the control group only (66%) (*P* < 0.001). There was also a relationship between the extent of cerebral hypoxaemia and increased length of stay.

However, this study can be criticised on several grounds. Firstly, the MMSE is not a very good discriminator of POCD. Secondly, changes in haemoglobin as a result of blood loss were not recorded. Thirdly, they resorted to the use of propofol to lower cerebral metabolic rate for oxygen (CMRO2) to improve rSO2 rather than using methods such as blood transfusion and optimization of fluid status to improve cerebral oxygen delivery. Nevertheless, they showed that in elderly patients undergoing major surgery there is a risk that falls in cerebral oxygenation may take place which could result in POCD. Overall, though, the incidence of POCD in the treatment arm was still high at 35%, higher than the overall figure of 26% in the ISPOCD1 trial.

b) Depth of anaesthesia and potential toxicity of anaesthetic agents

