**7. Hypotheses**

a)In an RCT, closer anaesthetic monitoring and anaesthetic management of patients during surgery will improve post-operative cognitive outcomes compared with patients receiving usual anaesthetic monitoring at 7 days and at 3 months post-operatively.

.

b)Twelve months post-operatively, overall cognitive performance and function on every day activities will be significantly more impaired in post-operative patients than in age matched controls.

c) Twelve months post-operatively the incidence of MCI and dementia will be significantly higher in post-operative patients than in age matched controls.

d) A fall in cerebral oxygenation >15% will be associated with a significant increase in the risk of POCD and strategies to correct or minimise this fall with reduce the incidence of POCD

e) Minimisation of cumulative deep anaesthetic time will reduce the incidence of POCD

f) Genes predisposing to dementia, attentional impairments, delirium and abnormal NOS activity will increase the risk of POCD.

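### Hypothesis a spans seven cognitive scores at two visits, but the protocol names no primary outcome or visit, ties its power statement to no measure, and calls any two-sided p below 0.05 significant

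*Protocol*

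**What the plan says.** - **Hypothesis.** Section 7, hypothesis a, predicts that closer monitoring and management will improve cognitive outcomes, in the plural, "compared with patients receiving usual anaesthetic monitoring at 7 days and at 3 months post-operatively".
- **Measures.** Section 8, Assessments, lists a global score and a memory score, "section B (CAMCOG-B - , Mini-Mental State Examination -MMSE), memory (CAMCOG memory subscale"), followed by Trail Making A, Trail Making B, vigilance accuracy and vigilance reaction time. That makes seven scores, taken before surgery and at 1 and 12 weeks after it.
- **Significance rule.** Section 8, Statistical methods: "Two-sided p values of less than 0·05 will be deemed to be statistically significant".
- **Power.** The same paragraph says "The study is powered as a pilot study" and "A cohort of 73 patients gives 80% power to the 5% level of significance to detect a between group difference of 0·33 SD". It names neither the measure nor the visit to which the 0.33 SD applies.
- **Use of the word primary.** In the Statistical methods it describes the efficacy population only, not an outcome.
- **What is deferred.** A full statistical evaluation protocol is to be written by the study statistician. For POCD itself, "Definitions of POCD and other criteria for cognitive dysfunction will be validated based upon an initial cohort study (appendix 1").

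**The concern.** A trial's 5% error rate belongs to a defined claim. Here the claim is improved cognitive outcomes, and the protocol does not say which score, at which visit, would establish it. As written, a significant difference on any one of the seven scores at either visit could be presented as support for hypothesis a, and nothing in the protocol limits that choice to one made before the results are known.

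The power statement has the same gap. A standardised difference of 0.33 can be judged only for a named score at a named visit, since the scores will differ in variability, in correlation with baseline and in how far they can be expected to move.

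**Working it through.** **1. The plan's own figure.** The inputs are a difference of 0.33 SD, 80% power and a 5% two-sided level. The one-sample or paired formula gives ((1.960 + 0.842)/0.33)² = 72.07, which rounds up to the stated 73. The comparison of two independent arms needs twice that number in each arm: 2 × 72.07 = 144.1, so 145 per arm and 290 in total. With 73 patients in total, an unadjusted two-arm comparison has about 29% power. The stated 73 therefore does not reproduce for a between-group difference without some further assumption, and with no outcome named there is nothing against which to check one.

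**2. Number of comparisons.** Seven scores (Assessments) × two post-operative visits (hypothesis a and Assessments) = 14 between-arm comparisons. This is the number that the significance rule permits. The protocol does not say that all 14 will be tested.

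**3. If success on any one may be claimed, with independent tests and no true effect.**
- Either direction: 1 − 0.95^14 = 0.512.
- Favouring the intervention only: 1 − 0.975^14 = 0.298.

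**4. With correlated tests.** Fourteen standard normal statistics with a common correlation r were simulated, one million draws per setting, with the cut-off at 1.96. The values of r are assumptions.

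| r | Any significant result, either direction | Any significant result favouring the intervention |
|---|---|---|
| 0 | 51.2% | 29.9% |
| 0.3 | 43.8% | 22.5% |
| 0.5 | 34.8% | 17.5% |
| 0.7 | 24.8% | 12.4% |
| 0.8 | 19.7% | 9.8% |
| 0.9 | 14.1% | 7.1% |

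The nominal rates are 5% and 2.5%. Separate correlations between measures and between visits give similar values: 38% in either direction with both at 0.5, and 28% with both at 0.7.

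**5. If improvement at both visits is required.** With independent tests, the chance that at least one score is favourably significant at both visits is 1 − (1 − 0.025²)^7 = 0.4%. If a different score may serve at each visit, it is (1 − 0.975^7)² = 2.6%. Simulation over between-measure correlations of 0 to 0.8 and between-visit correlations of 0 to 0.7 gives about 0.3% to 7% across these two definitions.

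**6. After the change.** One named outcome at one visit, tested at two-sided 0.05, has an error rate of 5%, of which 2.5% is in the favourable direction. One score tested at both visits without adjustment would have 1 − 0.95² = 9.75% if the visits were independent.

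**The case against.** **The later plan.** The sentence after the significance rule announces a full statistical evaluation protocol. A method for handling several tests is commonly left to such a document, so its absence here is no finding. That part of the objection stands. It does not cover the choice of primary outcome and visit, which defines what the trial tests and what its sample size refers to, and so belongs in the protocol.

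**The text does not specify 14 unadjusted tests.** This also stands. The rule says neither that each score will be tested nor that no adjustment will be made, and Assessments is a list of measurements rather than of analyses. The calculation shows what the wording leaves open.

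**The size.** A reader might take 25-51% as the chance of a false claim for hypothesis a. The documents do not support that: the hypothesis predicts improvement, and those figures also count results that favour usual care. Nor is 25% a floor, since it rests on an assumed correlation of 0.7. Independence is unlikely too, because the memory score is a CAMCOG subscale and the same patients are tested twice. The wording on 7 days and 3 months can also be read as requiring both visits, with the far lower rate shown above.

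**Pilot status.** This softens the consequence. It does not remove the significance rule, or the 80% power claim in the same paragraph.

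**The POCD definition.** A reader might infer that the Appendix 1 cohort cannot supply a usable definition, because its table shows only MMSE, simple reaction time and choice reaction time, and section 4 says "Firstly, the MMSE is not a very good discriminator of POCD". That goes too far. The table reports recovery rates for three measures without saying that no others were collected, and the remark on the MMSE criticises another study that relied on it.

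**Conclusion.** The point holds in this form: the protocol leaves the primary outcome and visit of its main hypothesis open, attaches its power statement to no measure, and sets a 0.05 rule that does not say which comparison it governs.

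On the any-of-14 reading, the chance of a false result favouring the intervention is about 5 to 12 times the nominal 2.5% for correlations from 0.7 down to 0, and still nearly three times at 0.9. These multiples depend on two things that the documents do not give: the correlations between scores and visits, and the rule that one favourable comparison is enough. If both visits must succeed, the inflation is small or absent. That the answer moves from under 1% to about 30% according to an unstated choice is the reason to state it.

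**What to change.** Before outcome data are seen, amend the protocol as follows.

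1. Name one primary cognitive outcome and one primary visit. One example is the mean z-score of the seven measures at 12 weeks, adjusted for baseline, with signs aligned so that higher is better. Other choices are defensible. Test it at two-sided 0.05.
2. Tie the power statement to that outcome and visit, and show the calculation for a comparison between two arms.
3. Treat the other visit and the individual scores as secondary, reported as estimates with 95% confidence intervals and no confirmatory significance claim, as suits a pilot. Any formal adjustment among them can be set out in the announced statistical plan.

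The cost is about a paragraph of text and no additional data collection. The downside is that fewer results can be labelled significant. The restated power calculation may also show that the planned enrolment supports only a larger detectable difference than 0.33 SD.
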